## Abstract

**Background:**

Women affected by adversity, including gender-based violence, are at increased risk for developing common mental disorders such as depression, anxiety and posttraumatic stress disorder (PTSD). The World Health Organization (WHO) has developed Problem Management Plus (PM+), a 5-session, individual psychological intervention program, that can be delivered by non-specialist counsellors that addresses common mental disorders in people affected by adversity. The objectives of this study are to evaluate effectiveness of PM+ among women who have been affected by adversity, including gender-based violence, and to perform a process evaluation.

**Methods:**

Informed by community consultations, the PM+ manual has been translated and adapted to the local context. A randomized controlled trial will be carried out in the catchment areas of three local health care facilities in Dagoretti Sub County, Nairobi. After informed consent, females with high psychological distress (General Health Questionnaire-12 (score >2) and functional impairment (WHO Disability Assessment Schedule 2.0 score >16) will be randomised to PM+ (n = 247) or enhanced treatment as usual (n = 247). Post-treatment and 3-months post-treatment follow-up assessments include psychological distress, functional disability, PTSD symptoms, perceived problems for which the person seeks help, health care use and health costs. For evaluating the process of implementing PM+ within local communities in Nairobi 20 key informant interviews will be carried out in participants, PM+ providers, decision makers, clinical staff.

**Discussion:**

If PM+ is proven effective, it will be rolled out to other low and middle income areas and other populations for further adaptation and testing.

*Trial registration* Australian New Zealand Clinical Trials Registry, ACTRN12616000032459. Registered prospectively on January 18, 2016

## Background

Gender-based violence (GBV) such as intimate partner violence or sexual violence by someone else is an increasing global topic of concern. Worldwide, the estimated lifetime prevalence of GBV is at least 30 % [1–3] Women living in urban poverty—including slums—in low and middle income countries (LMICs) are especially vulnerable for violence and common mental disorders, since poverty poses women at risk for experiencing gender-based violence. In Kenya, 47 % of women reported having experienced physical and/or sexual violence at some point in their lives.

Women exposed to GBV are at higher risk for developing common mental disorders such as depression, anxiety disorders, and posttraumatic stress disorder (PTSD) and make more use of health services than non-abused women [2, 4, 5]. Common mental disorders are among the largest contributors to disability and functional impairment (see Patel et al. [6]). Additional consequences of GBV involve reduced social and economic development prospects for women because of unwanted pregnancy, lack of resources, limited opportunities, concurrent physical health problems, low education, and fewer social supports [7, 8]. In most communities, women affected by GBV tend to receive no or minimal mental health support [1].

Effective interventions to treat common mental disorders are available (e.g., cognitive behavioural therapy; CBT [9, 10]). However, these interventions typically require expert mental health professionals providing treatments that are usually lengthy and costly to the health service. LMICs lack sufficient numbers of specialized mental health care professionals to deliver such interventions and are unlikely to afford costs associated with scaling up intensive treatment programs in an effective but safe manner. For practically and sustainably scaling-up evidence-based mental health care interventions in LMICs, interventions should be short and relatively easy to administer, so they can be carried out by non-specialist helpers in the community, such as community health workers (cf. [11]). In addition, interventions should not target one outcome (e.g. PTSD) but address a broader range of outcomes, including general functioning and common mental and psychosocial health problems.

World Health Organization (WHO) has developed a low-intensity 5-sessions program termed Problem Management Plus (PM+) which may be delivered by trained non-specialist helpers [12]. PM+ aims to reduce symptoms of depression, anxiety, PTSD, stress in the wake of adversity and trauma and to improve functioning. It comprises evidence-based techniques: of (a) problem solving, (b) stress management, (c) behavioral activation, and (d) accessing social support.

The impetus for developing the PM+ manual came from request to the Department of Mental Health and Substance Abuse at the WHO in Geneva to develop interventions for survivors of GBV that may be delivered in such manner that they are feasible in Sub-Saharan Africa, where (a) health systems typically do not have the resources to make available proven psychological interventions on a routine basis (e.g. exposure therapy, cognitive processing therapy, Eye Movement Desensitization and Reprocessing), and (b) where social stigma against GBV can be so high that attending specific mental health care for GBV can put women at social risk (e.g., further violence, abandonment by the community). PM+ addresses these two requirements by involving relatively simple, non-intrusive techniques that do not necessarily focus on the trauma of GBV. It can thus be offered outside of the context of vertical GBV-services by briefly trained but well-supervised helpers to most women impaired by distress, irrespective of the causes of the distress. Additionally, this study aims to test the capacity of PM+ to reduce mental disorders in women affected by GBV by screening for psychological distress in women in adversity-affected community settings; because this way of case identification potentially overcomes the barrier of GBV-survivors to seek mental health assistance and reduces the risks of stigmatizing women who have suffered GBV through services that are only for GBV survivors.

## Methods

### Aim and design

This study aims to evaluate the effectiveness of the locally adapted version of PM+ in women affected by adversity and GBV in urban slum areas in Nairobi, Kenya in reducing symptoms of common mental disorders. We will conduct a randomized controlled trial (RCT) comparing PM+ to enhanced treatment as usual (ETAU) in 494 study participants. See Fig. 1 for an overview of the design. In addition, we will perform a process evaluation to examine barriers and facilitators when implementing the RCT and the interventions in the chosen settings.

**Fig. 1 Fig1:**
[figure not shown]
Flow diagram

### Setting

The study will be carried out in three local health care facilities that are part of the primary healthcare system of the Dagoretti Sub County Nairobi in Kenya. Kenya is a LMIC; despite a growing middle class, almost half (45.9 %) of the population lives below the national poverty line. The study is overseen by staff of World Vision Kenya and their Riruta Area Development Program, which is a geographic area where World Vision implements long-term community development programs in collaboration with primary health care centres.

### Participants

Participant inclusion criteria are: (a) adult (18 years or older) females; (b) score above 2 on a screening questionnaire for psychological distress (General Health Questionnaire-12; GHQ-12; and (c) score above 16 on a screening questionnaire for functional impairments (WHO Disability Assessment Schedule 2.0; WHODAS; [13]). These instruments are described below. Exclusion criteria are: (a) male gender; (b) acute medical conditions; (c) risk of suicide; or (d) severe mental disorders or cognitive impairment (e.g., severe intellectual disability, dementia, psychosis).

### Informed consent

Informed consent entails a two-step procedure: (1) Informed consent for screening and (2) Informed consent for taking part in the PM+ trial. The latter is only required for participants meeting inclusion criteria. For each step respondents who decide to participate will be asked to complete a written consent form. Each person will be given at least 24 h to think whether she wants to take part in the PM+ trial. For participants who are illiterate, witnessed oral consent and a thumb print in lieu of a signature will be asked, in line with recommendations from WHO [14]. The witness will not be a member of the research team.

### Procedure

Participants will be included through community screening at the homes of the participants by independent assessors. Assessors start sampling at a central point in the community and randomly select a direction in which to screen, selecting households using a population-based interval approach. In this approach, members from a larger population are selected according to a random starting point and a fixed, periodic interval (called the sampling interval), which is calculated by dividing the population size by the desired sample size. Thus, the sampling interval will vary depending on the population size of each of the three areas involved in the research.

After selecting the households, independent assessors will identify and attempt to meet with the head of each household. The assessors explain the purpose of the survey and ask if they may interview a random adult woman aged 18 years or older from the household. If a household does not have a woman of 18 years or older, or the woman declines to be screened for the research, the enumerator moves on to the next household based on the sampling intervals.

The independent assessors will refer individuals meeting any of the exclusion criteria to specialist support in the county according to their need. All interviews are conducted face-to-face in a private space (e.g. in people’s homes or in a quiet area near their homes). If participants are not selected because they score below the cut-offs for either the GHQ-12 or the WHODAS, they will be provided feedback on their test outcomes and reasons why they are not eligible for the study will be explained to them. Next, the pre-assessment is completed by administering the PTSD Checklist for DSM-5 (PCL-5), Life Events Checklist (LEC), selected questions of the WHO violence against women instrument (WHO-VAW), the psychological outcome profiles instrument (PSYCHLOPS) and items derived from the Service Receipt Inventory (SRI).

The post-intervention assessment (WHODAS, GHQ-12, PCL-5, PSYCHLOPS) is scheduled 7 weeks after the pre-intervention assessment (i.e., 1 week after the 5th PM+ session), and the follow-up assessment (WHODAS, GHQ-12, PCL-5, LEC, PSYCHLOPS, SRI) is scheduled at 13 weeks after the post-intervention assessment (i.e. 20 weeks after inclusion, in line with the timing of the follow-up assessment for the PM+ participants). The participants who receive PM+ will also be administered the PSYCHLOPS by the non-specialist helpers at the beginning of each PM+ session. Table 1 presents an overview of measures that are administered at each of the assessments.

**Table 1 Tab1:** Overview of measures administered at the assessments

Concept	Pre-assessment measures	Post-treatment assessment measures	3-months post-treatment follow-up assessment measures
1. Psychological distress	GHQ-12 (*screener and primary outcome*)	GHQ-12	GHQ-12
2. Functioning	WHODAS (*screener*)	WHODAS	WHODAS
3. PTSD symptoms	PCL-5	PCL-5	PCL-5
4. Perceived problems	PSYCHLOPS	PSYCHLOPS	PSYCHLOPS
5. Adverse life events	LEC		LEC
6. Violence against women	WHO-VAQ		
7. Costs of care	SRI items		SRI items

All instruments will be delivered in interview format as many participants are expected to be illiterate. Female independent assessors, most holding a tertiary-level degree in psychology or a related discipline, and fluent in Kiswahili and English will carry out the screening and pre and post assessments. Assessors will have received a three-day training covering administering the instruments, common mental disorders, general interview techniques, and ethical research conduct. An additional one-day training in psychological first aid and how to support women experiencing emotional distress will also be provided for assessors. Ongoing monitoring of assessors’ competency will be conducted through regular supervision by the trial manager. The assessors will be blind to the allocation status of the participants.

### Sample size

A total number of 494 participants will to be included. Since we are not aware of intervention studies that have been carried out in this population, and we expect the population to be heterogeneous with respect to the types of common mental disorders, we aimed for a small to medium effect size of *d* = 0.04 in GHQ-12 symptom score in the PM+ group as compared to the control group at 3 months after the conclusion of the study. These estimates are in line with the observed effectiveness of an intervention led by lay health counsellors for depressive and anxiety disorders in a study in primary care in India [15]. Power calculations suggest a minimum sample size of 133 participants per group (power = 0.95, alpha = 0.05, two-sided). Taking into account 30 % attrition at follow-up, at least 346 participants (173 per group) need to be included. Further, since we estimate that 70 % of women in this distressed sample would have a history of GBV, we intend to include at least 494 women in the study.

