### Randomization

Randomization will occur following pre-assessment. This will be conducted by an independent research assistant located off-site (University of New South Wales) and not involved in any other aspects of the study. Randomization will be performed using computerized software on a 1:1 basis.

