### Analysis

To determine comparability between the conditions at baseline, multiple planned comparisons will be conducted for continuous variables and Chi squared tests for categorical ones.

Hierarchical linear modeling (HLM) analysis will be carried out to assess differential change over time in GHQ, WHODAS, and PSYCHLOPS scores between groups. For each outcome, the effects of time of measurement, group, and the group-by-time interaction will be analyzed. HLM presumes intent-to-treat analyses as HLM allows the number of observations to vary between participants and effectively handles missing data. Time (linear and quadratic), treatment condition, and their interaction will be included in the models. Fixed effects parameters will be tested at 95 %CI. The Level 1 model will represent within-patient change over time, and the Level 2 model will predict variation in within-patient change over time and encompass between-patient variables. Outcome analyses will be reported primarily in women reporting GBV, and secondarily for women affected by all forms of adversity.

Descriptive analyses will be carried out in SPSS and HLM analyses in Stata version 11.2. Across all analyses, two-tailed tests will be reported with *p* < 0.05.

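### The printed effect size (d = 0.04) and power (0.95) do not give 133 per group; 133 is the two-sided answer for d = 0.40 at power 0.90

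*Protocol article*

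**What the plan says.** The Sample size section of the protocol article sets the target in these words: "we aimed for a small to medium effect size of *d* = 0.04 in GHQ-12 symptom score". The comparison is between PM+ and control at 3 months. The error rates are given as "power = 0.95, alpha = 0.05, two-sided", and the result is "Power calculations suggest a minimum sample size of 133 participants per group".

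That number is the base of the enrolment target. The section allows for 30% attrition and states that "at least 346 participants (173 per group) need to be included". It then allows for 70% of the women having a history of gender-based violence (GBV) and arrives at 494.

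Two other sections fix the remaining inputs. Under Randomization: "Randomization will be performed using computerized software on a 1:1 basis". Under Analysis: "Across all analyses, two-tailed tests will be reported", at p < 0.05. The Analysis section also makes women reporting GBV the primary reporting population.

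**The concern.** One paragraph prints every input and the answer, and the answer does not follow. A standardised difference of 0.04 is not a "small to medium effect size", and 133 per group could not detect it. Moving the decimal point to 0.40 still does not give 133 at the stated power.

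The effect size and power are the trial's declared design properties, and they affect how its result is read. Someone told that the trial has 95% power would take a null result as missing the target effect 1 time in 20. At 133 per group and d = 0.40 it would be missed about 1 time in 10. Someone asking whether the observed effect met the target would have a benchmark ten times too small.

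**Working it through.** **Inputs.** Two-sided alpha 0.05, power 0.95, d = 0.04 and n = 133 per group (Sample size); 1:1 allocation (Randomization); two-tailed tests (Analysis). The value d = 0.40 is an assumption, printed nowhere, and inferred from the verbal description and from the 133.

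**Method.** With the SD set to 1, the normal approximation is n per group = 2(z₁₋α/₂ + z_power)² / d². The same quantities were computed with the noncentral-t two-sample test, which is slightly more exact. Here z₀.₉₇₅ = 1.960, z₀.₉₀ = 1.282 and z₀.₉₅ = 1.645, so (1.960 + 1.282)² = 10.507 and (1.960 + 1.645)² = 12.995 (unrounded quantiles).

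**Attempts to reproduce 133 per group**

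| d | Power | Sides | Normal approximation | t-test | Gives 133? |
|---|---|---|---|---|---|
| 0.04 (printed) | 0.95 | two | 2 × 12.995 / 0.0016 → 16,244 | 16,244.3 → 16,245 | No |
| 0.40 | 0.95 | two | 2 × 12.995 / 0.16 = 162.4 → 163 | 163.4 → 164 | No |
| 0.40 | 0.90 | two | 2 × 10.507 / 0.16 = 131.3 → 132 | 132.3 → 133 | **Yes, exactly** |
| 0.40 | 0.95 | one | 136 | 135.96 → 136 | No (close) |
| 0.44 | 0.95 | two | 2 × 12.995 / 0.1936 = 134.2 → 135 | 135.2 → 136 | No (close) |

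The one-sided row comes close but contradicts the two-sided statement in Sample size and the two-tailed rule in Analysis.

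**Power with 133 per group** (two-sided; normal approximation Φ(d√(n/2) − 1.960), with √(133/2) = 8.155)

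- d = 0.40: Φ(3.262 − 1.960) = Φ(1.302) = 0.904; t-test 0.901. The type II error is 1 − 0.901 = 9.9%.
- d = 0.04: Φ(0.326 − 1.960) = Φ(−1.634) = 0.051; t-test, counting both tails, 0.062.
- d detectable at 0.95 power: 3.605 / 8.155 = 0.442; t-test 0.444.

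**How the base carries forward.** 133 × 1.3 = 172.9, printed as 173 per group (346 in total); 346 / 0.7 = 494.3, printed as 494. The enrolment target therefore rests on the 133. Applying the plan's own losses to 494, the GBV analysis keeps 494 × 0.7 × 0.7 / 2 = 121 per group, with t-test power 0.87 at d = 0.40. The full sample after 30% loss keeps 494 × 0.7 / 2 = 173 per group, with power 0.96.

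**The case against.** - **The d = 0.04 is an obvious misprint.** The same sentence calls the effect small to medium, so the requirement of over 16,000 per group describes a slipped digit, not the design. That is fair, but a target effect wrong by a factor of 10 still needs correcting, and the repaired statement still fails on power.
- **The intended value may be 0.44, not 0.40.** One wrong digit would then explain nearly everything, because d = 0.44 with 133 per group gives power 0.947. This cannot be excluded. However, 0.95 power at d = 0.44 needs 136, whereas d = 0.40 at 0.90 gives 133 exactly.
- **The planned analysis is a longitudinal hierarchical model.** A baseline or repeated-measures gain could lower the requirement. Bringing 163 down to 133 needs 1 − r² = 133/163, so r is about 0.43. The article states no such gain, and a plain t-test reproduces 133 without one. It remains true that the 0.90 figure is conditional on that unnamed method.
- **The trial enrols 494, not 266.** The full sample after 30% loss has power 0.96 at d = 0.40, so the all-women comparison does reach the claimed level. This point stands for that comparison. It does not help the primary GBV population, where about 121 per group and power 0.87 remain.
- **The correction is only wording.** True, since conduct and analysis do not change. But the figures concerned are the stated basis of the sample size.

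**Conclusion.** The power statement is wrong as printed. No reading consistent with two-sided testing at 0.05 turns d = 0.04 and 0.95 power into 133 per group. If d = 0.40 was meant, 133 per group has power 0.90, not 0.95. The type II error is 9.9%, about double the 5% claimed, and 164 per group would be needed for 0.95. If 0.95 was meant, 133 per group supports it only for d of about 0.44.

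The power figures assume an unadjusted two-sample t-test with 1:1 allocation. That d = 0.40 was intended is an inference from the verbal description and the exact match. The conclusion that the printed figures contradict each other does not depend on it. The loss of GBV participants below 133 per group is a separate matter that adds to the error and does not offset it.

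**What to change.** Correct the Sample size section after checking the original calculation for the effect size, power and method used. Either of these wordings agrees with 133 per group at two-sided alpha 0.05:

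- target effect d = 0.40, with power 0.90; or
- power 0.95, with a target effect of d = 0.44.

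The first matches the 133 exactly and is the more likely original. Name the method (two-sample t-test, or a covariate-adjusted calculation with its assumed correlation).

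The cost is an erratum and a somewhat less favourable stated power or target effect, with no change in enrolment. If the sponsor did intend 0.95 power at d = 0.40, wording alone is not enough: the base becomes 164 per group, and the attrition and GBV steps must be recalculated from it. Whichever is chosen, the corrected text should make clear that the quoted power belongs to 133 analysed per group, since the primary GBV analysis is expected to have about 121.

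### The 30% attrition allowance multiplies by 1.3 instead of dividing by 0.7, so 494 women are expected to leave 121 GBV completers per arm, below the plan's minimum of 133

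*Protocol article*

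**What the plan says.** The Sample size section of the protocol article builds the total in three steps.

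1. Base size. It targets a "small to medium effect size of *d* = 0.04 in GHQ-12 symptom score" and reports that "Power calculations suggest a minimum sample size of 133 participants per group", with "power = 0.95, alpha = 0.05, two-sided".
2. Attrition. "Taking into account 30 % attrition at follow-up", it says that "at least 346 participants (173 per group) need to be included".
3. GBV share. Because "we estimate that 70 % of women in this distressed sample would have a history of GBV", it says that "we intend to include at least 494 women in the study".

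The Analysis section then fixes the population to which the calculation must apply: "Outcome analyses will be reported primarily in women reporting GBV, and secondarily for women affected by all forms of adversity". The Primary outcomes section places the GHQ-12 endpoint at 3-month follow-up, so the women who count toward the target are those with a GBV history who are still assessed at that visit.

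**The concern.** Steps 2 and 3 make the same kind of correction. In each, 30% of the women enrolled will not count (they drop out, or they have no GBV history), and the enrolled number must be large enough that the remaining 70% meets the target. Step 3 divides by 0.70, which is right. Step 2 multiplies by 1.30, which is too small. The two rules stand in consecutive sentences.

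The error carries through to 494, so the planned total does not deliver the plan's own minimum in the population reported first. A reader of a null result in women reporting GBV would take the comparison to have the stated size and power when it is expected to have less of both.

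**Working it through.** **Inputs, all from the Sample size section unless noted:** 133 per group; power 0.95; two-sided alpha 0.05; attrition 30%; GBV share 70%; total 494, which is 247 per arm (Abstract). The printed effect size is d = 0.04.

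**Reproducing the plan's chain**
- 133 × 1.3 = 172.9, rounded to 173 per group, 346 in total. This matches.
- 346 / 0.70 = 494.3, given as 494. This matches.

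**Checking the attrition step**
- Completers from 173 per group: 173 × 0.70 = 121.1, below 133.
- Number needed for 133 completers: 133 / 0.70 = 190 per group, 380 in total.
- 173 would suffice only if attrition were no more than 1 − 133/173 = 23%.

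**What 494 delivers**
- Women with GBV: 494 × 0.70 = 346.
- GBV completers: 494 × 0.70 × 0.70 = 242, or 121 per arm.
- All randomised completers: 247 × 0.70 = 172.9, about 173 per arm.
- Total needed to keep 133 GBV completers per arm: 266 / 0.49 = 543.

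These head-counts do not depend on the effect size or the test.

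**Which effect size**

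With n per group = 2(z₀.₉₇₅ + z_power)² / d²:
- d = 0.04, power 0.95: 2 × (1.960 + 1.645)² / 0.0016 ≈ 16,244 per group. This cannot be the basis of 133.
- d = 0.40, power 0.95: 2 × (1.960 + 1.645)² / 0.16 ≈ 163 (164 by the t-test).
- d = 0.40, power 0.90: 2 × (1.960 + 1.282)² / 0.16 ≈ 132 (133 by the t-test).

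I therefore assume that 0.40 was meant, which also suits the small-to-medium label. On that assumption 133 per group is the size for two-sided power 0.90, not 0.95.

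**Power at d = 0.40, two-sided alpha 0.05**

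The normal approximation is Φ(d√(n/2) − 1.960). For n = 121: 0.40 × √60.5 = 3.111, and Φ(1.151) = 0.875.

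| Completers per arm | What it represents | Normal approximation | t-test |
|---|---|---|---|
| 121 | GBV completers from 494 | 0.875 | 0.873 |
| 133 | stated minimum | 0.904 | 0.902 |
| 173 | all randomised completers from 494 | 0.961 | 0.960 |

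**Splitting the gap from 0.95 to 0.87**
- Attrition slip, 133 to 121 per arm: 0.90 to 0.87, about 3 points.
- Mismatch between 133 and the stated power, present before attrition: 0.95 to 0.90, about 5 points.

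**Sensitivity**
- If 133 is taken to give 0.95, the implied d is (1.960 + 1.645) × √(2/133) = 0.44. Power at 121 is then Φ(0.442 × √60.5 − 1.960) = 0.93, a loss of about 2 points.
- At the printed d = 0.04, power at 121 per arm is only about 0.05 to 0.06.

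**The case against.** Four things can be said for the plan.

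- The planned hierarchical linear model keeps women with partial data, so those who miss only the follow-up visit still contribute. This is fair, and it makes the completer-based power figures approximations. But counting completers is the basis the Sample size section itself uses when it allows for attrition, so the 121 against 133 comparison stands.
- The loss is small. At any effect size compatible with 133 per group, power at 121 per arm is about 0.87 to 0.93. That stands too, and it is why no design change is asked for.
- The 133 may come from a method the article does not describe. For example, adjusting for a baseline score that correlates about 0.43 with the outcome gives 163 × (1 − 0.43²) ≈ 133 at power 0.95. The article states no such correlation, and the attrition step would be wrong under any method.
- The total is worded as a minimum, so more women could be enrolled. But the Abstract and the design section fix 494, and the stated minimum is itself derived from the faulty step.

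A reader might infer that the attrition slip alone pulls power from 0.95 down to 0.87. The figures do not support that: correcting attrition would restore only about 0.90 at d = 0.40. A reader might also infer from the printed d = 0.04 that the trial has almost no power. The sample size and the verbal label both show that 0.04 was not the value used.

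**Conclusion.** The attrition step is wrong as printed: 173 per group should be 190 if 133 completers per group are required. With 30% attrition and 70% GBV history, 494 women are expected to give 121 GBV completers per arm, 12 short of the stated minimum in the population reported first. This part is certain on the plan's own inputs.

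The effect on power depends on d. Assuming 0.40, two-sided power is about 0.87, of which the attrition slip accounts for about 3 points relative to 0.90 at 133 per arm. The remaining 5 points or so to the stated 0.95 come from the separate mismatch between 133 per group and 0.95. If 133 is taken to give 0.95 (d = 0.44), power at 121 is 0.93.

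The finding does not show that 494 is inadequate overall: all randomised women give about 173 completers per arm and about 96% power at d = 0.40.

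**What to change.** Keep 494. Confirm the intended d, and correct the printed 0.04 if 0.40 was meant. Then replace the whole chain, from the 133 per group with its stated power of 0.95 through the 346 (173 per group), with what 494 delivers. Suggested wording, if d = 0.40 is confirmed:

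> With 70% GBV history and 30% attrition, 494 women give about 346 women with GBV and 121 GBV completers per arm, with about 87% power for d = 0.40 (two-sided alpha 0.05). All randomised women give about 173 completers per arm and 96% power.

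If 133 is kept for reference, label it as about 90% power at d = 0.40 and note that it would need 380 women with GBV (190 per group), or about 543 in total. Changing 346 to 380 while leaving 494 in place would not do, because 380 / 0.70 = 543. The new sentence would also clash with the old power of 0.95 and d = 0.04 if those were left standing.

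The cost is wording only. The stated power becomes less favourable; enrolment, design and analysis do not change.
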